# Study protocol: group-based psychoeducation for relatives of patients with bipolar disorder—a large scale real-world randomized controlled parallel group trial, the R-bipolar RCT

**DOI:** 10.1186/s13063-024-08172-z

**Published:** 2024-05-23

**Keywords:** Bipolar and related disorders, Caregivers, Caregiver burden, Psychosocial intervention, Family

## Abstract

**Background:**

Relatives of patients with bipolar disorder (BD) often experience emotional burden with stress and depressive symptoms that again increase the likelihood of destabilization and relapses in the patient. The effects of group-based psychoeducation have not been investigated in large-scale real-world settings. We are currently conducting a large-scale real-world randomized controlled parallel group trial (RCT) to test whether group-based psychoeducation for 200 relatives to patients with BD improves mood instability and other critical outcomes in relatives and the corresponding patients with BD.

**Methods:**

The trial is designed as a two-arm, parallel-group randomized trial with a balanced randomization 1:1 to either group-based psychoeducation or a waiting list for approximately 4 months and subsequent group-based psychoeducation. The primary outcome measure is mood instability calculated based on daily smartphone-based mood self-assessments. Other relevant outcomes are measured, including patients’ reported outcomes, assessing self-assessed burden, self-efficacy, and knowledge about BD.

**Discussion:**

This protocol describes our currently ongoing randomized controlled trial (RCT) that aims at investigating group-based psychoeducation as an intervention for relatives of individuals diagnosed with bipolar disorder (BD). The study is the first large-scale real-world RCT to focus on a relatively short intervention of psychoeducation (6 sessions of 2 h each) in a large group of relatives (approximately 30 participants per group). With this focus, we wish to test an intervention that is feasible to implement in real-life psychiatric settings with limited budgets and time. It is also the first study to use mood instability in relatives as the primary outcome measure and to investigate whether mood instability and other affective symptoms in patients and relatives covary. It could be considered as limitations, that the trial is not blinded and does not include long-term follow-up.

**Trial registration:**

ClinicalTrials.gov NCT06176001. Registered on 2023–12-19. The study is approved by the data agency (P-2021–809). The project was allowed to be initiated without permission from the Scientific Ethical Committees for the Capital Region, because it according to section 1, paragraph 4 of the Committee Act was not defined as a health scientific intervention study (case number 21063013).

**Supplementary Information:**

The online version contains supplementary material available at 10.1186/s13063-024-08172-z.

## Administrative information

Note: the numbers in curly brackets in this protocol refer to SPIRIT checklist item numbers. The order of the items has been modified to group similar items (see http://www.equator-network.org/reporting-guidelines/spirit-2013-statement-defining-standard-protocol-items-for-clinical-trials/).

## Introduction

### Background and rationale {6a}

#### Bipolar disorder—impact on patients’ lives

Bipolar disorder (BD) is a common psychiatric disorder with a prevalence of 1–2% and a substantial heritability of 60–80% [1]. It ranks among the six leading causes of disability worldwide because it has an early age of onset and a life-long course characterized by a high risk of recurrence of manic and depressive episodes [2], a lifelong elevated risk of suicide, and a decreased life expectancy of 8–12 years [3, 4]. Current treatments do not sufficiently improve overall prognosis and approximately half of the patients experience long-term mood symptoms oscillating between depressive and hypomanic/manic symptoms [5] that severely impact functioning and quality of life [6, 7].

#### Bipolar disorder—impact on relatives

It is well-established that being a relative to a person with a severe mental disorder is burdensome with negative impacts on quality of life, finances, and mental health [8–13]. Specific for BD is its episodic nature and diverse symptoms in depressive, euthymic, hypomanic, manic, and mixed episodes, respectively, which contribute to the burden for relatives [14]. Even when the patient is euthymic, relatives still experience distress related to the patient’s problem behavior, e.g., hyperactivity, irritability, and withdrawal [15, 16].

As BD has shown high levels of heritability [1], family members who are genetically associated with the person with BD, might carry a genetic predisposition for psychiatric morbidity. Partners to patients with BD also have a 3 to 8 times increased risk of psychiatric disorders, which is thought to be partly due to assortative mating [17].

#### The prognosis of bipolar disorder is affected by relatives

Relatives provide vital emotional and practical support for patients and are important partners in the collaboration around treatment [18, 19]. Indeed, lower levels of social support in patients with BD have been shown to increase the risk of recurrence of depression [20] and the risk of only reaching partial recovery [21]. The emotional environment in the family also affects the patient’s prognosis and high levels of “expressed emotions” (criticism, hostility, and emotional overinvolvement) are prospectively associated with relapses in affective disorders [22, 23].

#### Group-based psychoeducation—effects on relatives/caregivers of patients with BD?

In relation to patients with BD, group-based psychoeducation is a first-line recommendation for the treatment of BD as an effective intervention as shown in 18 randomized controlled trials reducing illness recurrences, number and duration of hospitalizations, treatment adherence, therapeutic lithium levels, and reducing stigma [24, 25].

Several studies have been published on psychoeducational interventions for individual families [26–28], but offering psychoeducational interventions for individual families is expensive and poses high levels of organizational difficulties [29]. Group-based psychoeducation can reduce costs and organizational challenges, but as shown in the following overview, research on group-based psychoeducation exclusively for caregivers is scarce and often characterized by small study samples and/or small psychoeducation group sizes which again decreases feasibility.

The “Barcelona Bipolar Disorder Program psychoeducational intervention for caregivers of bipolar patients” has shown promising results in two RCTs from 2004 [30] to 2008 [31], respectively. The program involved 12 weekly sessions of 90 min in groups of approximately 10 caregivers. The results suggest improved knowledge of the illness and reduced subjective burden among 45 caregivers [30] and fewer recurrences among 113 patients who lived with their caregiver [31]. The program is however rather long and the groups small, which makes it both costly for the clinic to provide and time-consuming for the relatives to attend.

Subsequent studies have tested the effects of shorter programs. A study, with a rather small study sample of 47 relatives, compared the effects of three groups: a multifamily group psychoeducation (5 sessions), a solution-focused group therapy (5 sessions), and treatment as usual (TAU), and found increased knowledge and reduced burden in both intervention groups compared with TAU [32]. Another study from 2015 tested the efficacy of a psychoeducation program of 7 sessions (each 2 h), for caregivers in groups of 10 participants. The intervention was found to advance family members’ knowledge about the illness, alleviate their burden, and reduce their distress [33].

A small study with 32 participants from 2016 showed promising results with a reduction of caregivers’ burden and increased self-efficacy and knowledge after a very short intervention with 2 × 150 min of group-based psychoeducation for caregivers only [34]. A recent study from 2021 studied the effects of psychoeducation in 8 sessions in groups of 8–10 caregivers and showed effects on reduced burden on the relatives and increased function and decreased symptoms in the respective patients with BD [35]. A feasibility study from 2021 tested a 7-week program but had challenges in recruitment and therefore a very small study sample of just 12 participants [36].

A meta-analysis combining data from 9 studies covering individual, family, and group-based psychoeducation suggested that psychoeducation might improve caregiver burden but also that larger and more well-designed trials are needed before clinical recommendations can be made [37].

In this study, we aim to test the effect of a large-scale group-based psychoeducation intervention that has already been implemented in our clinic (see later) for ten years. It has shown to be feasible and affordable due to the relatively large groups of relatives of approx. 20–40 participants.

### Objectives {7}

#### Objectives

To conduct a pragmatic randomized controlled trial (RCT) investigating whether group-based psychoeducation for relatives to patients with BD improves mood stabilization and other critical outcomes, in relatives and in patients with BD.

#### Hypotheses

*Primary:* group-based psychoeducation for relatives to patients with BD improves mood stabilization in *relatives*.*Secondary:* group-based psychoeducation for relatives to patients with BD improves other critical outcomes in *relatives* and mood stabilization and other critical outcomes in *patients with BD*.*Tertiary:* mood instability in patients and relatives covary.

### Trial design {8}

The trial is designed as a two-arm, parallel-group, superiority, randomized trial with a balanced randomization 1:1 to group-based psychoeducation versus a waiting list [38]. The control waiting list group will be offered participation in group-based psychoeducation (active intervention) during the following half year. The trial is planned and will be conducted in concordance with the CONSORT 2010 Explanation and Elaboration: updated guidelines for reporting parallel group randomized trials [39].

## Methods: participants, interventions, and outcomes

### Study setting {9}

The Copenhagen Affective Disorder Clinic is a large specialized mood disorder clinic with 18 full-time employees who provide treatment services for patients with newly diagnosed/first episode BD [40, 41]. The Copenhagen Affective Disorder Clinic receives patients from the entire Capital Region of Denmark covering a catchment area of 1.8 million people and all psychiatric centres in the region. Since 2010, Copenhagen Affective Disorder Clinic has provided large-scale group-based psychoeducation for relatives of patients with BD. Thus, we are investigating the effect of an intervention already implemented in real-world settings.

### Eligibility criteria {10}

Inclusion criteria: relatives of patients with BD who are affiliated with the Copenhagen Affective Disorder Clinic. It is the patients who decide which relatives they would like to invite for psychoeducation.Exclusion criteria: Insufficient Danish language, or age under 18 years.

Data from *patients* with BD are collected from the A-bipolar trial, which is another RCT that is currently running in the Copenhagen Affective Disorder Clinic [42].

### Who will take informed consent? {26a}

JRS contacts the relatives by phone and informs them about the study. If they wish to participate, JRS sends written information about the R-bipolar study. At the following inclusion interview, an informed consent is signed by both the participant and the investigator conducting the interview. This investigator will primarily be JRS, but in case of high work-load or sickness absence, other members of the research group, who are trained in the relevant clinically rated observer-based scores (HAM, YMRS, and FAST) will perform the inclusions, including obtaining informed consent.

### Additional consent provisions for collection and use of participant data and biological specimens {26b}

N/A, we do not collect biological specimens.

## Interventions

### Explanation for the choice of comparators {6b}

We have chosen to compare the group-based psychoeducation intervention with a control group on a waiting list. We aim to investigate and evaluate clinical practice in an ongoing real-world intervention in comparison with its actual alternative: no group-based psychoeducation. The two-armed parallel group randomization also makes it possible to optimize the data yield because participants who are randomized to the control group will also participate in the intervention group afterwards.

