### Intervention description {11a}

Group-based psychoeducation for relatives. Group size: 20–40 relatives. Duration of intervention: six sessions over 6–10 weeks, each session is 2 h long including a 15-min break. The sessions are held by experienced clinicians from the Copenhagen Affective Disorder Clinic, one chief physician, and one nurse. Each session focuses on a specific topic, which the clinicians present and discuss using a presentation viewer. The sessions are interactive, and the participants are encouraged to ask questions during the presentations. During each session, the participants will have some discussions in smaller groups to reflect on topics raised during the session.

The topics of the sessions are:Introduction (Information about the clinic, introduction of the clinicians and participants, expectations alignments)Bipolar disorder (the diagnosis and challenges in diagnosis)Medical treatment (which medication is used and why)Psychological treatment (psychoeducation for patients)Living with a bipolar disorder (a guest lecturer with lived experience with BD tells his own story of living with BD)Being a relative.

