**Fig. 1 Fig1:**
[figure not shown]
Spirit study schedule of enrolment, interventions, and assessments

*Primary outcome*: Daily self-reported mood instability collected via the Monsenso app^1^ [43] for relatives during the period in which the participants are part of the research project.*Secondary outcomes*: Other critically daily self-reported smartphone-based data including daily activity level, anxiety, irritability, stress, cognition, sleep, alcohol consumption, caregiver burden, and medicine as reported in [44].

Clinically rated observer-based scores on the following three scales: Hamilton Depression Scale-6 items (HAM-D6) [45] (being more sensitive in RCTs than the HAM-D17 [46]), the Young Mania Rating Scale (YMRS) [47] and the Functional Assessment Short Test (FAST) (a 24-item interviewer-administered interview concerning autonomy, occupational functioning, cognitive functioning, financial issues, interpersonal relationships and leisure time) [48].

Self-assessed scores on the following questionnaires: Burden Assessment Scale [49], Perceived Criticism Measure [22, 50], Carer Quality of Life [51, 52], Carer-Self-Efficacy [34, 53], Bipolar Knowledge Scale [54], Short Form-12 [55, 56], Brief Symptom Inventory [57], Perceived Stress Scale [58], Mood Disorder Questionnaire [59], Major Depression Inventory [60, 61], Childhood Trauma Questionnaire (CTQ) [62]. When the questionnaires are repeated after the intervention, the.

participants are asked to complete a satisfaction survey on the psychoeducation. The satisfaction survey was developed in close collaboration with the clinicians from the Copenhagen Affective Disorder Clinic.

*Tertiary outcomes*: Automatically smartphone-generated data on physical [63], and social activity [64].

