## Statistical methods

### Statistical methods for primary and secondary outcomes {20a}

#### Statistical analyses

Analyses will be conducted for the total sample of 200 relatives and their corresponding patients with BD. Two-level linear mixed-effect models will be used including a fixed effect of group (active group versus control) and a person-specific random effect allowing for individual variation in mood instability or other outcome measures.

In relation to hypothesis 3, it will be investigated whether mood instability in patients and relatives covary more than mood instability in patients and healthy control individuals (controls collected as part of the ongoing Bipolar Illness Onset (BIO) study in the Copenhagen Affective Disorder Clinic [77].

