## Trial status

Recruitment began on April 7th, 2022 and so far (January 5th, 2024) a total of 185 relatives have been included in the trial and 25 have dropped out. Recruitment is expected to be completed at the end of January 2024 and final data gathering will be finished in May 2024.

Protocol version 1.

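### The plan argues for using control relatives' data after their wait and does not confine the primary outcome window to the randomised waiting period

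*Protocol article*

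**What the plan says.** Trial design {8} declares a two-arm, parallel-group superiority trial, 1:1, and adds: "The control waiting list group will be offered participation in group-based psychoeducation (active intervention) during the following half year". The abstract gives the control condition as "a waiting list for approximately 4 months and subsequent group-based psychoeducation".

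Explanation for the choice of comparators {6b} gives a second reason for the design, namely that it "makes it possible to optimize the data yield because participants who are randomized to the control group will also participate in the intervention group afterwards".

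Outcomes {12} defines the primary outcome as daily self-reported mood instability "for relatives during the period in which the participants are part of the research project". The text gives no end day for controls. The schedule is in Figure 1, which is not available here.

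Estimation of mood instability, under {20a}, combines the squared successive differences over follow-up into one rMSSD per participant. Statistical analyses {20a} names a group effect (active versus control) and a person-specific random effect. It names no period or time term. Section {17b} refers to randomisation status as intervention versus control.

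The course is "six sessions over 6–10 weeks, each session is 2 h long including a 15-min break" ({11a}). Under Trial status, recruitment began in April 2022 and was expected to end in January 2024, and "final data gathering will be finished in May 2024".

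**The concern.** A control relative's later course raises the data yield only if data from that course are used. In a parallel-group comparison those data add nothing to the randomised contrast, because by then both arms have been offered the course. The reason given in {6b} therefore conflicts with the design in {8}.

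Taken with an outcome window that lasts as long as participation and a model with no period term, the wording leaves two ways for such data to reach the primary analysis:

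- **Left under control.** Days during or after the course count in the control arm, and the contrast shrinks.
- **Coded as active.** The same person supplies a control value and a later active value. Part of the group coefficient then becomes a before-after comparison within controls, open to time in study, season and habituation to daily self-rating.

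In both cases the controls concerned are selected by entry date and retention. The choice between the two could also be made after the data are seen.

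**Working it through.** The plan gives no figure of its own on this point, so there is none to reproduce. The checks below size the two routes.

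**1. Can controls supply course data before data gathering closes?** The last recruits enter in January 2024, and about 4 months of waiting takes them to May 2024, when data gathering ends. They supply little or none. A control who entered in April 2022 could wait 4 months, start as late as the end of a following half year, and take a 10-week course. That is 4 + 6 + about 2.3 = 12.3 months, ending around April 2023. So some controls can supply course data, but not all.

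**2. Treated days left under control.** Four months is about 17.3 weeks. For a control who rates through a full course, the course share of days is:

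- 6-week course: 6 / (17.3 + 6) = 26%
- 10-week course: 10 / (17.3 + 10) = 37%

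If the full effect is immediate and rMSSD averages roughly linearly (both assumed), that person's contrast shrinks by the same share. If 25–75% of controls do this (assumed), the arm-level dilution is 0.25 × 26% = 6% up to 0.75 × 37% = 28%.

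As an illustration of power, take the planned difference of 0.2 and 63 per arm ({14}), with an assumed SD of 0.4, the value at which 126 in total gives 80% power. {14} itself states an SD of 2.6, which does not return 126; that is a separate matter. With 10% dilution the difference is 0.18 and power 71%. With 20% it is 0.16 and power 61%.

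**3. Control course data coded as active.** Assumptions:

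- n = 80 per arm (Trial status: 185 included less 25 dropouts = 160, split equally)
- no true effect, and values in SD units
- within-person correlation r = 0.5–0.7
- a share q = 25–75% of controls add a later value coded active and shifted by a drift d

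Generalised least squares with a random intercept and no period term gives, per n:

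- A11 = 2 − q + 2q/(1+r)
- A12 = 1 + q/(1+r)
- A22 = 1 + q/(1−r²)
- D = A11·A22 − A12²
- share of d entering the group coefficient = [A11·q/(1−r²) − A12·q/(1+r)] / D
- SE = √[A11 / (n·D)]

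| q | r | Share of drift | SE | Type I error, d = 0.1 SD | Type I error, d = 0.2 SD |
|---|---|---|---|---|---|
| 0.25 | 0.5 | 0.35 | 0.136 | 5.8% | 8.2% |
| 0.25 | 0.7 | 0.48 | 0.121 | 6.8% | 12% |
| 0.50 | 0.5 | 0.55 | 0.121 | 7.3% | 15% |
| 0.50 | 0.7 | 0.68 | 0.103 | 10% | 26% |
| 0.75 | 0.5 | 0.67 | 0.112 | 9.2% | 22% |
| 0.75 | 0.7 | 0.78 | 0.091 | 14% | 40% |

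Worked case, q = 0.25 and r = 0.5: A11 = 2.083, A12 = 1.167, A22 = 1.333, D = 1.417. The share is (2.083 × 0.333 − 1.167 × 0.167) / 1.417 = 0.35. With d = 0.1 the estimate is 0.035 and z = 0.035/0.136 = 0.26, so the two-sided rejection rate is 5.8% instead of 5%.

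**The case against.** The strongest reply is that no passage says control relatives are recoded as active or pooled into the primary comparison. {6b} says only that they later take part in the intervention group and that this helps the data yield, which would also fit a separate before-after analysis. {8} declares parallel groups, {17b} speaks of randomisation status, and one rMSSD per participant does not fit a model in which a control has both a control and an active value. This stands, and it makes the recoding route the less likely one. It does not close the window, so treated days under control remain possible.

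Figure 1 may set an end of app use for controls. If it does, {12} and {6b} still need to agree with it. The January to May 2024 interval does match the wait, but only for those recruited last. {11c} places the question on sessions attended in the final questionnaire after psychoeducation and does not limit it to the active arm, which is compatible with controls staying in the project through their own course.

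It may also be said that cut-off dates belong in a fuller analysis plan. That would answer mere silence. Here the article states a reason that favours using the data and a window that admits them.

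The objection to extreme sizes also stands. Having every control contribute course data would give larger figures, but the recruitment dates rule that out, so they are not used. The documents give no drift, so 0.1–0.2 SD is only an illustrative range.

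**Conclusion.** The point holds as a conditional one. The text implies that control data from after the wait may be used and does not restrict the primary outcome to the randomised wait. A reader might infer that controls are definitely to be counted a second time in the intervention group, or that the randomised contrast is already compromised. The documents do not support either reading.

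Dilution is the likelier consequence: up to 26–37% for a control who rates through a full course, and less across the arm because only some controls can do so. A gradual rather than immediate effect would make it smaller still. The recoding route is less likely but more harmful, because it gives false positives rather than lost power. Under the assumptions above, its low end is barely above the nominal 5% and its high end is about 40%. The two routes are alternatives and do not add up.

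This should be corrected before analysis. Confidence is medium, because the schedule figure is not available here.

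**What to change.** - In {12} and {20a}, close each control relative's primary and secondary outcome window at the end-of-wait assessment or the day before the first session of their own course, whichever is earlier.
- Analyse all data within that window by randomised arm.
- Report controls' course-period data only as a separately labelled, uncontrolled before-after analysis, never pooled into the active arm.
- Reword the data-yield sentence in {6b} to match, and check that Figure 1 shows the same closing point.

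The cost is wording and a date cut in the app export. It needs no new participants or data, and it does not change whether or when controls are offered the course. The downside is that control course data no longer add to the main comparison. The sample size in {14} does not count on them.
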